### 11.7.3. Safety Analysis

#### Study-related Adverse Events

Adverse events will be coded according to coding dictionaries (the web based MedDRA version current at the time of coding) with relationship determined by the investigator. AEs will be classified by system organ class and preferred term. AE data will be listed individually, and each AE (based on preferred terminology) will be counted only once for a given participant. If the same AE occurs on multiple occasions, the highest severity and least complimentary relationship will be assumed. If two or more AEs are reported as a unit, the individual terms will be reported as separate experiences. Adverse events will be summarised based on the ITT analysis population and will be summarised descriptively by group by frequencies along with associated percentages.

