|                                           | 
surgeon will take a cavity shave of the corresponding margin, provided more tissue can be taken.
 
All LightPath® images will be acquired within approximately 145 minutes post-injection.
 
The WLE specimen and cavity shavings (where performed) will undergo standard of care histopathological analysis.
 
Participants will return for a study completion visit, coinciding with their standard of care surgical follow-up for the MDT decision whether to re-operate (1-2 weeks after completion of the initially planned surgery).
                                                                                                                                                                                                                                                                                                                                                                        |
| Data Analysis for Outcome Measures | 
All patients who pass screening will be included in the intention to treat (ITT) population.
 
The per protocol (PP) population is defined as all patients who completed BCS and study procedures as per protocol description.
 
The primary endpoint will be analysed based on the PP population.
 
The secondary endpoints will be analysed using the PP population and the ITT population.
 
The primary analysis of the study, including analysis of all available study outcomes (primary, secondary and exploratory where data is available), will be conducted after all patients have completed the follow-up visit.
 
Subgroup analysis will be conducted to assess the impact of important subgroups (e.g., breast cancer subtypes, invasive/in situ) on the performance of intraoperative LightPath® CLI + FAR imaging.
 
All outcome measures will be summarised descriptively.
 |

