## **8.8. Study Duration**

### **8.8.1. Duration of Subject Participation**

The point of enrolment in the study is the point at which the subject provides written informed consent and participation in the treatment phase ends at the conclusion of surgery. Adverse events will be recorded until discharge, or for 24 hours after the first study procedure, whichever is sooner. Participants will return for a study completion visit at the time of the MDT decision whether to re-operate (1-2 weeks after completion of the initially planned surgery).

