## **10. Adverse Events Definition and Reporting**

### **10.1. Adverse Event Definition**

An adverse event (AE) is any untoward medical occurrence in a participant or participant administered a pharmaceutical product (or surgery in this study) and which does not necessarily have a causal relationship with this treatment. An AE can therefore be any unfavourable and unintended sign (including an abnormal laboratory finding), symptom, or disease temporally associated with the use of a

medicinal product as part of a clinical study, whether or not related to the medicinal product (or surgery).

All AEs, either observed by the Investigator or reported by the participant, must be reported immediately, and no later than 24 hours of becoming aware of the event, to the Sponsor. To report an AE, the Principal Investigator (PI) will complete an AE report form or other relevant form located in the Case Report Form. The report will include the following information: nature, severity, date of onset, duration, course and history of the adverse event/adverse device effect and causality.

Recording of AEs will begin with the commencement of the first study procedure. As all study procedures are completed prior to the end of surgery and the radiopharmaceuticals have short physical half-lives, AE recording will conclude when the subject is discharged from hospital, or 24 hours following the first study procedure (whichever is sooner). Any adverse event identified in this period considered by the Principal Investigator (PI) to be related to a study procedure will be followed until resolution or for 30 days, whichever is sooner.

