### 10.6. Adverse Event Reporting

AEs occurring from the first study procedure until the end of follow-up will be reported by completing the relevant section of the CRF. AEs judged by the CI to be related to the standard care of the participant and unrelated to any study procedure do not require to be reported.

The following information will be recorded in the adverse event section of the CRF:

- The signs, symptoms, or diagnosis of the event
- The date and time of onset and resolution of the event
- The adverse event severity using the criteria outlined above
- The relationship of the event to the study procedures as outlined above
- The seriousness of the event as outlined above;
- A list of any required therapy, medication, treatment, or diagnostic procedure
- Any additional data which might be relevant to the event.

The CI is responsible for the appropriate medical management of all adverse events and for the personal safety and wellbeing of the participants.

In addition, a positive sterility test result post-release for a batch which has been administered to patients will be classified as an Adverse Event of Special Interest (AESI). For this reason, infections that could be signs and symptoms possibly related

to bacterial endotoxin will be considered AESI and be immediately reported to the Sponsor even if non-serious. All AESI must be reported in the same manner as SAE reporting and will be handled in the same way.

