### 11.6. Data Analysis

#### 11.6.1. Analysed Population

All participants enrolled into the study will be assigned to the following analysis sets:

- The intention to treat (ITT) analysis set. This will comprise all patients assigned to treatment.
- The Per Protocol analysis set. This set will comprise all participants who complete the study according to the protocol and who were compliant with assessment procedures (i.e., completed follow-up visits in accordance with local practice). It includes only those participants whose WLE specimens, and cavity shavings (if any) specimens were imaged within the time-window of approximately 145 minutes post-injection.

Further sensitivity analysis and summaries will be conducted based on sub-sets of the per protocol analysis set: e.g., subsets based on breast cancer diagnosis prior to surgery (invasive/DCIS), age etc.

A summary of the rate of decision to re-operate in the “Delayed LightPath® image set” (any participant for whom LightPath® Image of WLE and any cavity shaving specimens is outside the optimal time-window) will be presented as these participants will be excluded from the per protocol analysis set.

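### Adverse event percentages use an ITT denominator that does not require exposure, so they can only be understated; the effect is small and conditional

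*Protocol*

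**What the plan says.** Section 11.7.3 of the protocol names the population for the adverse event summary: "Adverse events will be summarised based on the ITT analysis population". It also fixes the measure: events "will be summarised descriptively by group by frequencies along with associated percentages". A denominator is therefore needed, and the ITT set supplies it.

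The ITT set is defined twice. The synopsis states: "All patients who pass screening will be included in the intention to treat (ITT) population". Section 11.6.1 states: "This will comprise all patients assigned to treatment". The sentence that introduces the sets in 11.6.1 reads "All participants enrolled into the study will be assigned to the following analysis sets", and section 8.8.1 places enrolment at consent: "The point of enrolment in the study is the point at which the subject provides written informed consent".

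The recording window opens later. Section 10.1 states: "Recording of AEs will begin with the commencement of the first study procedure". Section 10.6 gives the same start: "AEs occurring from the first study procedure until the end of follow-up will be reported". The schedule of events in section 2.4 agrees, marking adverse events on the day of surgery, at discharge and at study completion but not at screening.

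Section 8.9 allows withdrawal at any time. Section 11.8 anticipates that about 10% of participants will drop out or not be evaluable for the primary endpoint, without replacement.

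**The concern.** The numerator and the denominator follow different rules. An event can enter the numerator only once a study procedure has begun. A woman enters the denominator earlier, on passing screening or on being assigned to treatment. A woman who qualifies and then withdraws, or whose operation is changed, before any study procedure adds one to the denominator and by construction nothing to the numerator. Her zero means that nobody was recording. It does not mean that she was observed and had no event.

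The direction is fixed: such women can lower the percentages but never raise them. This matters somewhat because section 10.3 already expects no adverse events from the radiopharmaceuticals and holds that the device cannot be linked to any. The adverse event table is the check on that expectation, and its denominator should not err only in the favourable direction.

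The two ITT definitions are a related defect. They could give two values of N for the same table. Section 11.7 uses the same set for the secondary outcomes, and section 11.7.1 uses it for a sensitivity analysis of the primary outcome.

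**Working it through.** **Inputs from the protocol.** Planned enrolment is 60, to leave 54 in the analysis (11.6.2). Anticipated drop-out or non-evaluability is about 10% (11.8). The protocol gives no figure for women lost before the first study procedure. Call that number u. It is an assumption, shown here over a range.

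**The plan's own figure.** 54 / (1 − 0.10) = 60, so the stated enrolment is reproduced.

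**Formula.** Let e women have a given adverse event and let N be the size of the ITT set.
- Percentage under the plan: e / N
- Percentage among women who started a study procedure: e / (N − u)
- Ratio of the first to the second: (N − u) / N, which does not depend on e

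**Results for N = 60 and e = 6** (10.00% under the plan in every row):

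| u | N − u | Ratio | Among women who started |
|---|---|---|---|
| 0 | 60 | 1.000 | 10.00% |
| 1 | 59 | 0.983 | 10.17% |
| 3 | 57 | 0.950 | 10.53% |
| 6 | 54 | 0.900 | 11.11% |

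At u = 6, three events read 5.00% instead of 5.56%, and twelve read 20.00% instead of 22.22%.

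**Alternative reading of the sample size.** Section 11.8 also says that recruitment continues until up to 60 women have been imaged. If 60 start a procedure and 10% are lost beforehand, 60 / 0.90 = 66.7, so about 67 pass screening and u = 7. The ratio is 60 / 67 = 0.896, essentially the same ceiling.

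**Why u = 6 (or 7) is a ceiling.** The 10% in section 11.8 combines drop-out with non-evaluability for the primary endpoint. Section 11.6.1 excludes from the per protocol set any woman whose specimens were imaged outside the time window. Those women were injected and operated on, their adverse events are recorded, and they are not part of u.

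**The case against.** The strongest reply is that the effect may be nil and is small in any case. It needs at least one woman who passes screening and then starts no study procedure. Women who fail the eligibility criteria are stopped under section 8.4 and do not meet the synopsis definition. The analysis is mostly descriptive, and section 11.7.3 also lists events individually, so counts are unaffected and a reader who knows how many were exposed can recompute any percentage. All of this stands, and it is why the point is minor.

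It does not remove the point, because the protocol does not leave the denominator open. It names one that is not tied to exposure.

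A reader might infer more than the text supports:
- **That women injected but not imaged are also wrongly counted.** They have started a study procedure, their events are recorded, and they belong in the denominator.
- **That a 10% understatement is to be expected.** The 10% is not a figure for losses before exposure.
- **That a safety claim or confidence bound is compromised.** The protocol plans no safety hypothesis and no confidence limit for adverse events.
- **That assignment to treatment in 11.6.1 must mean enrolment at consent.** This is one reading for a single-arm study with no described assignment step. It could also mean women taken forward to the intervention. Neither reading expressly requires that a procedure was started.
- **That the lack of a safety set is a separate fault.** Such a set is often defined in the SAP, which is not shown. The fault is the rule that section 11.7.3 does state.

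**Conclusion.** The point holds as a minor one. Section 11.7.3 puts adverse event percentages on a set that can include women for whom recording never began, so any error is downward. The factor is 1 with no such woman, 0.983 with one in 60 and 0.95 with three. It is about 0.90 at most if the whole anticipated 10% were lost before any study procedure. At that ceiling, six events read 10.0% instead of 11.1%, a difference of 1.1 percentage points.

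The size rests on the assumed number of such women, which the protocol does not give. The direction rests only on the stated definitions and the stated start of recording. The primary analysis, which uses the per protocol set, is not affected. The disagreement between the two ITT definitions is present in the text whatever u turns out to be.

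**What to change.** - In section 11.7.3, replace the ITT population with a safety set: all participants who started any study procedure, meaning those who received any study radiopharmaceutical, whether or not surgery or imaging was completed.
- Tie that set to the same event that starts recording in sections 10.1 and 10.6. A set limited to women who received 18F-FDG would not match. Sections 4.2.2 and 8.6.1 place the 99mTc tracer before 18F-FDG. If the tracer injection counts as the first study procedure, a woman with a recordable event after it whose 18F-FDG was not given would be dropped.
- List participants with no study procedure separately, with the reason.
- Make the ITT definition identical in the synopsis and section 11.6.1.

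The cost is about two sentences in the protocol, carried into the SAP, with no new data, procedures or participants. The one downside is that adverse event percentages may become slightly less favourable.

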### 11.8. Termination / Drop-out

Recruitment will continue until up to 60 participants have been imaged. It is anticipated that approximately 10% of participants may drop out of the study or not be evaluable for the primary endpoint. The sample size of  $n = 54$  for the primary endpoint was selected including allowance of the assumption of 10% drop out. No other provision has been made for participant drop out. Patients who drop out will not be replaced.

## 12. Statement of Compliance

This clinical study will be conducted in accordance with the Declaration of Helsinki (2013), ICH Harmonized Tripartite Guideline for Good Clinical Practice R2 (2017), BS EN 13612:2002 and all applicable local and national regulations.

This clinical study may not commence at any study site until all required approvals / favourable opinions for that study site have been obtained from the appropriate institution, Ethics Committee and Competent Authorities (where applicable). Any additional requirement imposed by the Ethics Committee or Competent Authority shall be followed.

A copy of the written notification of study approval and associated documents, detailing statement of compliance, will be stored in the Clinical Trial Master File and the Investigator Site File. The CI agrees to promptly report to the institution

(hospital/clinic) and Ethics Committee all unanticipated problems involving risks to human participants or others.

### **12.1. Insurance**

The study is co-sponsored by King's College London (KCL) and Guys and St Thomas' NHS Foundation Trust (GSTT). The sponsors will, at all times, maintain adequate insurance in relation to the study. KCL through its' own professional indemnity (Clinical Trials) & no fault compensation and the GSTT having a duty of care to patients via NHS indemnity cover, in respect of any claims arising as a result of negligence by its employees, brought by or on behalf of a study participant.

## **13. Quality Control and Quality Assurance**

Investigators who participate in this clinical study and who sign the study documentation will seek to ensure that all participants included in the study are compliant with the requirements of the study at the point of entry and remain so during their participation in the study.

Repeated and serious failures in participant compliance will be addressed as they have the potential to affect both patient safety and study outcome and where necessary corrective and preventative actions will be taken.

## **14. Protocol Amendments**

The CI agrees not to make any changes to, or deviate from, the protocol except when necessary to eliminate immediate hazards to human life.

Changes in the protocol may be made only by written amendment by the sponsor. Protocol amendments must be approved by the Ethics Committee and, if appropriate, the Competent Authority before implementation. Documentation of approval for such amendments must be stored in the Clinical Investigation Master File and the Investigator Site File.

### **14.1. Procedure for Reporting Deviations from the Protocol**

All deviations from the protocol must be recorded and reported to the sponsor. A Protocol Deviation Form must be completed for each study protocol deviation. An Investigator must notify the sponsor and the Ethics Committee of any significant deviation from the protocol that was done to protect the life or physical wellbeing of a subject (medical emergencies). Such notice should be given within 24 hours of the emergency occurring.

## **15. Device Accountability and Storage**

A LightPath® Imaging System has been procured from LightPoint Medical Ltd. and is stored in a safe and secure location within the KCL and GSTT premises, according to local guidelines. Regular electrical safety checks will be performed by the GSTT MEMS department, following the local regulations. LightPoint Medical Ltd. will perform system maintenance as and when required.

